## Statistical considerations

### Randomization

This study will employ a 1:1 randomization between Arm 1 and Arm 2, with further stratification by centre. Permuted block randomization will be used to reduce selection bias, promote allocation concealment, and improve balance across groups over the trial period. Participants will be randomized based on computer-generated random permuted blocks using a block size based on a multiple of 2 (with the block size known only to statistician until analysis is completed). This is an open-label randomized controlled study design, however, outcome assessors and data analysts will be blinded to the identity of each treatment arm.

The Coordinating Centre will be responsible for randomization of participants using a randomization module in the REDCap Electronic Data Capture (EDC) system, which will be used for trial data collection. In conjunction with trial statistician and Site Principal Investigators, the Coordinating Centre will be responsible for storing and analyzing trial data.

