## Study design

This is a phase II open-label randomized controlled trial using a 1:1 randomization between two arms (26 Gy in 5 fractions vs. 13 Gy in 1 fraction PBI). Participating institutions will include the six BC Cancer sites. The trial schema is shown in Fig. 1.

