## Interventions

*Standard Arm—Multiple Fraction PBI (Arm 1)*.

Participants on Arm 1 will be treated with PBI with a dose of 26 Gy in 5 daily fractions.*Experimental Arm—Single Fraction PBI (Arm 2)*.

Participants on Arm 2 will be treated with PBI with a dose of 13 Gy in 1 fraction.

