### Follow-up evaluation and assessment of efficacy

After treatment, participants will be followed up after 2 weeks. Clinical follow-up appointments will then be scheduled at 2 months, 6 months, 12 months, 18 months, and 24 months, and may be conducted via telephone or videolink. Follow-up visits requiring a physical exam may still be conducted via telephone/videolink if the physical exam is performed within the specified window by the participant’s Family Practitioner (FP) or General Practitioner in Oncology (GPO), with documentation. Otherwise, the participant must return to the clinic for the physical exam to be performed on-site. At each visit, a medical history will be conducted by the oncologist, and CTCAE toxicities recorded using the adverse events form, as well as ECOG scores. The POSI-Breast questionnaire is to be completed at baseline and on each follow-up visit.

A mammogram will be done beginning 6 months after treatment, then annually thereafter. Cytological or histological confirmation of the ipsilateral and contralateral primary tumor is required, including at the time of recurrence.

There is no planned follow-up at the end of the study. Additional care or follow-up assessments that will be provided to participants after they complete or discontinue the study will involve standard of care treatment for what is normally expected for their condition.

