### Data safety monitoring committee (DSMC)

The DSMC will be made up of the study co-investigators and will review data relating to safety and efficacy to ensure the continued scientific validity and merit of the study. If the DSMC deems that toxicity rates are excessive (> 25% grade 3, or > 5% grade 4 or 5 toxicity), then the DSMC can, at its discretion, recommend cessation of the trial, dose adjustment, or exclusion of certain subsets of the study population that are deemed as high-risk for complications.

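### The unqualified claim that outcome assessors are blinded cannot hold for PRO-CTCAE and POSI-Breast, and conflicts with how CTCAE assessment is described

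*Protocol article*

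**What the plan says.** The Study design section states: "This is a phase II open-label randomized controlled trial using a 1:1 randomization between two arms". The Randomization section repeats the open-label label and attaches a blinding claim to it: "outcome assessors and data analysts will be blinded to the identity of each treatment arm". It does not say which outcomes, which assessors or what method of masking is meant.

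Other sections describe how the subjective outcomes are obtained:

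- **PRO-CTCAE.** The opening of Methods describes it as toxicity that participants report themselves. Under Secondary Endpoint(s) it is collected during treatment and at six later times, from 2 weeks to 24 months.
- **POSI-Breast.** This is a questionnaire completed at baseline and at each follow-up visit. The Inclusion criteria require participants to be able to enter their own reported outcomes, alone or with help.
- **CTCAE.** Methods describes it as rated by a health provider, and Secondary Endpoint(s) gives the same timing as for PRO-CTCAE. The follow-up section states: "At each visit, a medical history will be conducted by the oncologist, and CTCAE toxicities recorded using the adverse events form".

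**The concern.** Assessor blinding matters most for outcomes that rest on judgement or self-report. Here the two regimens differ in a way that nobody taking part can miss, and the outcomes most open to expectation are rated by participants or by providers. Expectation could favour the convenient single visit, or it could make raters wary of a large single dose.

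Methods sets out to compare toxicity and quality of life between the arms. A reader, or someone later assessing risk of bias, who took the Randomization sentence at face value would credit those contrasts with blinded outcome assessment. On the article's own description, they do not have it.

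**Working it through.** No arithmetic is involved beyond a count. The check sets the blinding sentence against the assessment procedure for each outcome.

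**Step 1: can the arm be hidden from the participant?** The Interventions section gives, for the standard arm, "Participants on Arm 1 will be treated with PBI with a dose of 26 Gy in 5 daily fractions" and, for the experimental arm, "Participants on Arm 2 will be treated with PBI with a dose of 13 Gy in 1 fraction". The number of attendances reveals the arm. The design is declared open-label, so no attempt to hide it is implied.

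**Step 2: go through the seven secondary endpoints.**

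| Secondary endpoint | Source of the assessment | Can the blinding claim hold as written? |
|---|---|---|
| POSI-Breast | Participant | No, for all six post-treatment times. The baseline form may precede allocation; the article does not say |
| PRO-CTCAE | Participant | No, at any time |
| CTCAE | Health provider, during treatment and at follow-up visits | In conflict with the description (step 3) |
| Local control | Histology | Not contradicted; masked pathology reading is possible |
| Overall survival | Death from any cause | Assessor masking hardly matters |
| Progression-free survival | Progression at any site, or death | Ascertainment is not described in enough detail to say |
| CT simulation to radiotherapy | Dates | No rating is involved |

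The count of affected endpoints is 3 of 7.

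**Step 3: CTCAE in two parts.** During treatment, a provider grading toxicity is dealing with a course of one day or of five daily fractions, and its length gives the arm away. At follow-up, the article places CTCAE recording in the same visit, and the same sentence, as the oncologist's history-taking. It mentions no separate masked rater or central adjudication. That the oncologist does the grading is the natural reading, but the sentence is passive and names no recorder. The follow-up limb is therefore a conflict with the procedure as described, whereas the participant-reported limb is an impossibility.

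**Step 4: data analysts.** The same sentence also covers data analysts. Nothing elsewhere in the article contradicts that part, since analysis on coded arms is compatible with everything stated.

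**The case against.** The strongest reply has three parts.

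*The sentence itself says open-label, and a journal article leaves masking details to the full protocol.* The first half is right: the article does not claim that participants or treating staff are masked. The full protocol may also name a separate CTCAE rater. But the point is not that detail is missing. The article makes a positive, unqualified claim, and no fuller document can turn a participant's own report into a blinded assessment. This reply softens the CTCAE follow-up limb and leaves the participant-reported limb untouched.

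*The consequence is small.* This largely stands. The primary endpoint is the number accrued. Statistical methods provides only descriptive reporting for POSI scores and adverse events, with a formal test for PFS and OS alone. The Discussion makes the phase III trial depend on feasibility, not on toxicity or quality-of-life contrasts.

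*It is easy to read too much into this.* That is a fair warning, on four counts:

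- A reader might infer that no blinding exists in this trial. The text does not support that: blinded analysts and masked pathology reading remain possible.
- A reader might infer from "In conjunction with trial statistician and Site Principal Investigators, the Coordinating Centre will be responsible for storing and analyzing trial data" that Site Principal Investigators see arm labels. Shared responsibility does not show this. The article does not say that they treat trial participants; Trial management gives them eligibility review. Nor does running the randomization module rule out coded analysis.
- A reader might add that the safety committee consists of co-investigators. Committee membership is a separate matter from masking outcome assessors.
- A reader might want to list the remaining outcomes as safe from unmasking. The article does not establish that either: the simulation-to-treatment interval depends on scheduling, and histologic recurrence on who is referred for biopsy, and both can depend on a known arm.

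**Conclusion.** The blinding sentence is wrong as written for PRO-CTCAE and POSI-Breast, and inconsistent with CTCAE as the article describes it. That is three of seven secondary endpoints. The participant-reported part needs no assumption beyond the declared open-label design and the two schedules. The CTCAE part rests on reading the follow-up sentence in its natural sense, and on course length being evident to whoever grades toxicity during treatment.

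The practical effect is moderate. Contrasts in subjective, descriptively reported outcomes could be presented, or later cited, as blinded when they are not. Neither the size nor the direction of any bias can be identified from the document, and no analysis of these data can remove it. The primary accrual endpoint is unaffected. The finding does not extend to analyst blinding or to local control.

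**What to change.** Rewrite the blinding sentence in the Randomization section so that it does four things:

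1. It states that PRO-CTCAE, POSI-Breast and CTCAE as currently described are open-label assessments, and that their between-arm contrasts will be reported as such.
2. It limits the blinding claim to those who can actually be masked: data analysts working on arms coded A and B until the analysis is locked, and pathology reading of recurrence if that reading is masked.
3. It specifies that any Site Principal Investigator who takes part in the analysis receives coded output only.
4. If the full protocol does provide a masked CTCAE rater for follow-up, it says so, identifies the role, and reconciles this with the follow-up section. On-treatment CTCAE would still be labelled open-label.

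The cost is wording, plus coded output where site investigators join the analysis. No additional assessor or visit is needed, and neither the primary endpoint nor the sample size changes. The one drawback is that the stated design becomes slightly less favourable.

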### Number of participants/sample size

The study aims to enroll 60 participants in at least 4 out of 6 BC cancer centres. The sample size of 60 participants was selected based on feasibility across multiple sites and to allow for meaningful descriptive analyses.

### Statistical methods

Descriptive statistics will be used to report the number of participants accrued, descriptions of participant characteristics, time interval from CT simulation to plan approval, POSI scores, and rates of local control and adverse events.

PFS and OS will be calculated using the Kaplan-Meier method with differences compared using the stratified log-rank test.

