**Methods:**

This is a phase II randomized controlled trial, with a primary objective of testing the feasibility of randomizing participants to 1 vs. 5 fractions of PBI for early stage, node negative, breast cancer. The primary endpoint is the ability to accrue 60 participants at 4 of the 6 BC Cancer centres over a 2- year period and to randomize them to 1 vs. 5 fractions of radiotherapy for PBI. Its secondary endpoints are time from CT simulation to partial breast radiotherapy, local control rates, quality of life as measured by Prospective Outcomes and Support Initiative (POSI)-Breast, rates of provider-rated toxicities as measured by Common Terminology Criteria for Adverse Events (CTCAE), rates of participant-reported toxicities as measured by participant reported outcome version of CTCAE (PRO-CTCAE), overall survival, and progression-free survival.

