Initial studies on single-fraction (SF) radiation for PBI have investigated its safety and effect on cosmetic outcomes. A phase I/II single arm prospective clinical trial has confirmed that a SF dose of 20 Gy of radiation delivered 2 to 8 weeks after lumpectomy is a well-tolerated therapy that does not adversely impact cosmesis or quality of life as reported by physicians and participants [14]. Another phase I trial has demonstrated that SF PBI can be employed to safely increase the dose up to 30 Gy in a SF with low toxicity and without detriment to baseline cosmesis [15]. Although longer follow-up would be needed to confirm efficacy results, initial tumor control data from these studies are promising.

Like other medical services in Canada impacted by the ongoing health care crisis, cancer radiation treatment wait-lists are continually growing. This presents a systemic need for efficient and accessible treatments. Employing a single fraction for PBI is one promising radiation technique that could reduce wait times and improve access to radiation. Participants with early stage, node negative breast cancer will benefit from a shorter course of radiotherapy that will save them time and money. The regimen will also be particularly advantageous for participants from rural and remote communities, who must travel long distances to receive high quality cancer care. This phase II trial of SF PBI vs. multiple fraction PBI is therefore proposed.

The standard arm will use a dose of 26 Gy in 5 fractions, which has been adopted in the province for PBI. This dose fractionation is based on data from the FAST-Forward trial and extrapolation of its results alongside the findings of IMPORT-Low, a partial breast radiation trial that used 40 Gy in 15 fractions [9, 13, 16]. 

In the experimental arm, this study will investigate a single-fraction PBI dose of 13 Gy. A similar single-fraction dose has been used in CT-guided high-dose-rate brachytherapy for breast intraoperative radiation therapy. A phase I trial by Showalter et al. [17] and its subsequent phase II trial [18] both utilized 12.5 Gy, a dose that was found to be feasible and safe.

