## Methods

The objective of this phase II randomized controlled trial is to test the feasibility of randomizing participants to 1 vs. 5 fractions of partial breast irradiation (PBI) for early stage, node negative, breast cancer. It also aims to collect data on the time from CT simulation to partial breast radiotherapy, and to compare toxicity, local control, quality of life (QoL) as measured by POSI-Breast, health provider rated toxicity as measured by Common Terminology Criteria for Adverse Events (CTCAE), participant self-reported toxicity as measured by participant reported outcome version of CTCAE (PRO-CTCAE), overall survival (OS), and progression free survival (PFS), between the two arms.

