### Secondary Endpoint(s)

The secondary endpoints of the study are the following:

Time from CT simulation to partial breast radiotherapy.

Measured as the time from the day of CT simulation to the first fraction of PBI for Arm 1 or day of single-fraction PBI for Arm 2.

Local control rates.

Local control measured as the absence of ipsilateral in-breast recurrence, defined as histologic evidence of invasive or in situ breast cancer in the ipsilateral breast.

Quality of life.

Assessed using the Prospective Outcomes and Support Initiative (POSI) for Breast Data questionnaire, administered at baseline, then at 2 weeks, 2 months, 6 months, 12, months, 18 months, and 24 months post-treatment.

Rates of provider-rated toxicities.

Occurrences of adverse events as measured by CTCAE assessed during treatment then at 2 weeks, 2 months, 6 months, 12, months, 18 months, and 24 months post-treatment.

Rates of participant-reported toxicities.

Occurrences of adverse events as measured by PRO-CTCAE assessed during treatment then at 2 weeks, 2 months, 6 months, 12, months, 18 months, and 24 months post-treatment.

Overall Survival (OS).

Time from randomization to death from any cause, or last follow-up, whichever occurs first. [Time Frame: approximately at the end of year 2 (study completion)]

Progression-free survival (PFS).

Time from randomization to disease progression at any site, death, or last follow-up, whichever occurs first. [Time Frame: at 6 weeks, 6 months, 12 months, 18 months, and approximately at the end of 24 months]

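### The statistical methods report the interval from CT simulation to plan approval, whereas the secondary endpoint as defined runs from CT simulation to treatment

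*Protocol article*

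**What the plan says.** Three places in the protocol article give the same timing endpoint.

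- Abstract, Methods: "Its secondary endpoints are time from CT simulation to partial breast radiotherapy".
- Methods, opening paragraph: the trial aims to "collect data on the time from CT simulation to partial breast radiotherapy".
- Secondary Endpoint(s), first item: "Time from CT simulation to partial breast radiotherapy". It is defined operationally as "the time from the day of CT simulation to the first fraction of PBI for Arm 1", or to the "day of single-fraction PBI for Arm 2".

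The Statistical methods section is the only place in the article that states how endpoints will be analysed. Its list of items for descriptive reporting gives the timing item as the "time interval from CT simulation to plan approval". It does not mention the interval to the first or only fraction.

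**The concern.** The endpoint section and the analysis section name two different variables. Plan approval is a planning milestone and the first fraction is delivery of treatment. An analyst who follows the Statistical methods section would report how long planning took, not how long the participant waited from simulation to treatment.

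This matters because waiting time is part of the case for the trial. The Background says: "Employing a single fraction for PBI is one promising radiation technique that could reduce wait times and improve access to radiation". Of the listed endpoints, the simulation-to-treatment interval is the only one that measures a wait for treatment. With two end events in print, it is also unclear which interval was prespecified, and a later report could present either one with apparent support from the protocol.

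**Working it through.** There is no stated figure to reproduce. The check is a comparison of definitions, followed by simple algebra on what the difference can do.

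**Side by side**

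| Place in the protocol article | Start | End |
|---|---|---|
| Abstract, Methods | CT simulation | Radiotherapy |
| Methods, opening paragraph | CT simulation | Radiotherapy |
| Secondary Endpoint(s) | Day of CT simulation | First fraction (Arm 1) or single fraction (Arm 2) |
| Statistical methods | CT simulation | Plan approval |

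**Could the two end events be the same thing under different names?** No. The Secondary Endpoint(s) section ties the end to a day of treatment, separately for each arm. The Quality assurance section requires contour peer review before treatment and physics checks of every plan, so the document itself treats preparing a plan and delivering it as separate steps. Plan approval appears nowhere else in the article, whether as an endpoint, an objective or a defined milestone, so no other text links it to the day of treatment.

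**What is left out.** For one participant let

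- A = time from CT simulation to plan approval (the variable in Statistical methods),
- W = time from plan approval to the first or only fraction, with W ≥ 0 when the plan is approved before treatment,
- T = time from CT simulation to the first or only fraction (the endpoint as defined).

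Then T = A + W, and the share of the endpoint that is dropped is W / (A + W). The document gives neither A nor W, so this share has no value that can be derived from it. It is zero if W = 0 and grows with W.

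**What this does to the comparison of arms.** Taking means by arm, the difference in T equals the difference in A plus the difference in W. If W is the same on average in both arms, the between-arm difference is unchanged and only the level of the interval is understated. If W differs by arm, the difference in A misses that part. The document does not say which case applies.

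**What does not depend on it.** The primary endpoint is accrual and randomization of 60 participants over 2 years. The sample size section bases the 60 on feasibility and descriptive analysis, not on this interval. The article ties progression to phase III to the feasibility of randomizing.

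**The case against.** The strongest reply is that this is one discrepant phrase in a one-sentence list in a condensed article. The endpoint is stated consistently three times, once with a full definition by arm, and the Methods section commits the trial to collecting it. A statistical analysis plan may exist and may use the right interval. The endpoint is one of seven secondary endpoints in a feasibility trial, is reported descriptively, and carries no test, stopping rule or stated decision.

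Most of that stands, and it limits the point in four ways.

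- A reader might infer that the wait for treatment will not be analysed at all. The document does not support that. It says the interval will be collected, and an analysis plan that is not shown may cover it. What can be said is that the methods as written state no analysis of it.
- A reader might want to put a percentage on the lost time. Any such figure would rest on assumed durations for both steps, because the document gives none.
- A reader might infer that the between-arm result would be distorted. That follows only if the time from approval to treatment differs between arms, on which the document is silent. Nor does it describe the workflow or any queue between approval and treatment.
- The Background's argument is about system-wide waiting lists. An interval that starts at CT simulation captures only part of that, whichever end event is used.

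What does not stand is the suggestion that this is merely detail left to an analysis plan. The article is not silent on the point; it names a different variable. An analysis plan that follows Statistical methods would carry the wrong interval forward, and one that follows Secondary Endpoint(s) would contradict the published methods. Either way the text needs correcting.

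**Conclusion.** The concern holds as an internal contradiction. The Statistical methods section names an interval that is not the defined secondary endpoint, leaves out any time between plan approval and treatment, and states no analysis of the endpoint as defined. The conclusion rests on the text alone and on plan approval being distinct from delivery of the first fraction; it needs no assumed durations.

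The size of the omission cannot be derived from the document. Severity is moderate: a descriptive secondary endpoint is misnamed where its analysis is described, while the primary feasibility endpoint, the sample size of 60 and the other analyses are untouched.

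**What to change.** In Statistical methods, replace the plan-approval interval with the endpoint as defined under Secondary Endpoint(s): days from CT simulation to the first fraction in Arm 1, or to the single fraction in Arm 2, reported descriptively by arm. If planning turnaround is also of interest, keep the simulation-to-approval interval as a separately named additional measure, so that the two cannot be confused. If a statistical analysis plan exists, check that it uses the same end event. A formal between-arm comparison is not needed to resolve the contradiction.

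The cost is one line of wording, best changed before outcome data are seen. It has no effect on treatment, visits or sample size. The article does not say explicitly that treatment dates are recorded, but this is a reasonable inference: the trial aims to collect this interval, and its follow-up visits are timed from treatment.

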### Patient discontinuation / withdrawal

A participant may voluntarily withdraw from the study at any time at his/her own request. Participants may also be withdrawn at any time at the discretion of the investigator if any exclusion/inclusion criteria have been violated during the study, they are unable to meet the mandatory planning requirements after enrollment, or for safety reasons, etc.

At the time of discontinuing from the study, if possible, an early discontinuation visit must be conducted. The clinical evaluations that would have been performed at the end of the study should be obtained. If a participant is removed because of an adverse or serious event, they should remain under medical observation as long as deemed appropriate by the treating physician and follow recording and reporting requirements.

Participants withdrawn or discontinued can be replaced at the discretion of the sponsor-investigator/Study Principal Investigator.

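### Local control is planned as a descriptive rate with no time origin, time point or allowance for incomplete follow-up, while PFS, which contains the same recurrences, gets Kaplan-Meier

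*Protocol article*

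**What the plan says.** All references are to the protocol article.

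- **Statistical methods.** Descriptive statistics cover accrual, participant characteristics, the planning interval, the POSI questionnaire, and "rates of local control and adverse events". The next sentence is "PFS and OS will be calculated using the Kaplan-Meier method with differences compared using the stratified log-rank test". Local control is not in it.
- **Secondary Endpoint(s).** "Local control measured as the absence of ipsilateral in-breast recurrence, defined as histologic evidence of invasive or in situ breast cancer" in the ipsilateral breast. No time origin, time point or end-of-observation rule follows. PFS and OS, in the same list, each run from randomization to the event or last follow-up and carry a time frame. PFS counts progression at any site, so an ipsilateral recurrence is a PFS event.
- **Methods (opening paragraph).** Local control is among the outcomes to be compared between the arms.
- **Patient discontinuation / withdrawal.** "A participant may voluntarily withdraw from the study at any time". A discontinuation visit with the end-of-study evaluations is sought where possible, and withdrawn participants may be replaced.
- **Follow-up evaluation and assessment of efficacy.** Visits run to 24 months after treatment. "A mammogram will be done beginning 6 months after treatment, then annually thereafter". No study follow-up is planned beyond the end of the study.

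**The concern.** Local recurrence is a time-to-event outcome, and follow-up here can end early. The article recognises this for PFS and OS but gives local control, whose events are a subset of the PFS events, a plain rate listed beside adverse events. Without a time point and a rule for participants who leave early, the rate has no fixed meaning. Two analysts could take the same 60 participants and divide by all randomized, by those who completed follow-up, or by those assessed at some visit, and each would be following the text.

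If the simplest choice is made (recurrences divided by everyone randomized), time after withdrawal is treated as recurrence-free and the two-year recurrence risk comes out too low. The report could then show a local control figure and a PFS curve built on different conventions for the same events. The trial is meant to lead to a phase III non-inferiority trial, so a clearly defined local control estimate is worth having even when events are few.

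**Working it through.** The article states no recurrence rate, dropout rate or event count for local control, and the 60 participants are justified by feasibility and descriptive analysis. There is no figure of the plan's own to reproduce, so what follows illustrates size only.

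**Inputs**
- N = 60, allocated 1:1, so about 30 per arm (article).
- Last visit at 24 months after treatment (article).
- Two-year recurrence p = 1%, 2% or 3% (assumed).
- Loss to follow-up by 24 months d = 10% or 20% (assumed).
- Constant hazards for both, and loss independent of recurrence (assumed).

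**Step 1: proportion over all randomized, against the true two-year risk.** Let a = -ln(1 - p) and b = -ln(1 - d) be the cumulative hazards over 24 months. The expected observed proportion is

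a/(a + b) × [1 - (1 - p)(1 - d)].

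Kaplan-Meier with independent censoring targets p itself.

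Example, p = 2% and d = 20%: a = 0.0202, b = 0.2231; 0.0202/0.2433 × (1 - 0.98 × 0.80) = 0.0830 × 0.216 = 1.79%.

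| True p | Expected events in 60 | Observed, d = 10% | Observed, d = 20% | Relative shortfall |
|---|---|---|---|---|
| 1% | 0.6 | 0.95% | 0.90% | 5% to 10% |
| 2% | 1.2 | 1.90% | 1.79% | 5% to 10% |
| 3% | 1.8 | 2.85% | 2.69% | 5% to 10% |

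**Step 2: in events.** The smallest shortfall is 0.05 × 0.6 = 0.03 events and the largest 0.10 × 1.8 = 0.18 (0.186 before rounding the percentage), both among 60 participants. In percentage points this is 0.05 to 0.3.

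**Step 3: scale.** One recurrence in an arm of 30 moves the rate by 1/30 = 3.3 points. With 0 of 30, the exact two-sided 95% upper limit is 1 - 0.025^(1/30) = 11.6%. The shortfall is small beside either.

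**Step 4: imaging schedule.** Mammograms fall at 6, 6 + 12 = 18 and 18 + 12 = 30 months after treatment. Only the first two lie within 24 months, so months 18 to 24 have no scheduled mammogram. The expected recurrences in that window are 60 × [(1 - p)^0.75 - (1 - p)] = 0.15, 0.30 and 0.44 for p = 1%, 2% and 3%.

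This gap is separate from the choice of estimator. If recurrences were found only at the two mammograms, a true 2% would show as 1.5% even with no loss, and Kaplan-Meier would also show 1.5%. PFS is affected in the same way.

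**The case against.** The strongest reply is that the article does not commit to anything wrong. A descriptive rate can be a Kaplan-Meier or cumulative-incidence estimate, and denominators and censoring rules are commonly left to an analysis plan that is not shown here. This stands in part: the missing detail alone would be no finding. What remains is that the section does assign methods endpoint by endpoint, and it gives Kaplan-Meier to PFS and OS while leaving local control with the descriptive items.

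A reader might go further and infer that the rate is crude, and that withdrawn participants, or those without a mammogram after month 18, count as recurrence-free. The documents do not support that. No sentence sets the denominator or says how such participants are handled. Nor does lack of a mammogram mean lack of assessment. Recurrence is defined by histology, and visits with a medical history continue to 24 months. A visit that requires a physical examination can be remote only if the examination is done and documented elsewhere, and end-of-study evaluations are sought at discontinuation. The article does not list which visits require the examination.

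A reader might also take the OS time frame, which places study completion at about the end of year 2, as a calendar cut. With uniform accrual over two years, a simple proportion would then show about half the two-year risk, a shift of up to about 1.5 points at 3%. The visit schedule runs to 24 months after treatment for each participant, so that reading is uncertain and the figure should not be relied on.

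It is also fair to say that few events are expected and that the primary endpoint is feasibility. That limits the importance of the point without removing it.

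**Conclusion.** The point holds as a minor improvement to a stated analysis choice. Local control is given a descriptive rate with no origin, time point or allowance for incomplete follow-up, while PFS, which includes the same ipsilateral recurrences, is given Kaplan-Meier. If the rate were computed over everyone randomized, it would understate two-year recurrence by about 5-10% in relative terms, well under one event in 60. That size rests on an assumed 1-3% two-year risk, 10-20% loss, constant hazards and non-informative loss. It does not touch the primary endpoint.

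The absence of a scheduled mammogram after 18 months is a real limit on any 24-month figure. It applies equally to PFS and is not cured by changing the estimator, so it is a matter for transparent reporting and gives no reason to prefer one endpoint's method over the other's.

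**What to change.** In Statistical methods, take local control out of the descriptive list and add a sentence to this effect: local control will be estimated by arm, from randomization, using Kaplan-Meier or the cumulative incidence of ipsilateral breast recurrence with death as a competing event, with a 95% confidence interval at 24 months; participants without recurrence are censored at their last documented disease assessment (clinical examination or imaging).

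Three details matter.

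- **Censoring date.** Do not use last contact, which credits time in which the breast was not assessed. Do not use the last mammogram alone either: it would nearly empty the risk set after month 18, so a recurrence found clinically in months 18 to 24 would be set against very few participants and the 24-month recurrence estimate would be biased upward.
- **Number assessed.** Report, by arm, how many participants have a documented assessment at the stated time point, and note that the last scheduled in-study mammogram is at 18 months and that PFS shares this limitation.
- **No events in an arm.** At 1-3% risk an arm of 30 has no recurrence with probability 0.99^30 = 0.74 to 0.97^30 = 0.40, and the usual Greenwood interval then has zero width. Name an interval that works in that case, such as an exact binomial limit on the number assessed.

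The cost is a short addition to the analysis text and a slightly wider, less favourable estimate. No visit or imaging is added. It does require that assessment dates be recorded. The imaging schedule itself is left to the sponsor.
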